## Abstract

**Background/Objectives:** Myalgic Encephalomyelitis/Chronic Fatigue Syndrome (ME/CFS) and Post-COVID Syndrome (PCS) are chronic conditions that share relevant pathophysiological mechanisms. Conventional rehabilitation programs have often been associated with patient dissatisfaction and frequent adverse events (AEs), highlighting the need for safer and more effective clinical approaches. This study aims to compare the effects of a telerehabilitation program based on conscious movement with those of conventional low-intensity exercise in individuals with ME/CFS or PCS. **Methods:** This is a prospective, single-blind, three-arm, parallel, superiority randomized clinical trial. A total of 147 participants (aged 18–70) with ME/CFS or PCS will be recruited and randomly assigned to one of three groups: (a) conscious movement; (b) low-intensity exercise; or c) usual care. All interventions will be delivered via telehealth over 12 weeks, with weekly 45-min sessions combining health education and individually tailored exercises. Participants will be encouraged to practice daily using the provided materials. Adherence rates and potential AEs will be recorded. The primary outcome is the total score on the 14-item Chalder Fatigue Scale at 12 weeks (post-intervention). Secondary outcomes include heart rate variability, functional performance, pain intensity and interference, mental health, interoceptive awareness, quality of life, sleep quality and fear of movement. Measurements will be collected at baseline, post-intervention, and at 3-month follow-up. **Discussion:** Recent evidence suggests that both autonomic and cognitive activity modulate immune function. Conscious movement, which integrates exercise with interoception and mindfulness-based strategies, may provide greater benefits than low-intensity exercise alone. Study limitations should be considered when interpreting the results. **Trial registration:** Registered at ClinicalTrials.gov on 15 May 2025 (NCT06978582). Protocol version 4 (29 September 2025). Ethics Committee code: 2025-0180.

## 1. Introduction

Myalgic Encephalomyelitis/Chronic Fatigue Syndrome (ME/CFS) is a chronic condition characterized by severe, medically unexplained fatigue [1], which imposes major socioeconomic costs by limiting daily function and work capacity [2]. Patients frequently report feeling misunderstood by healthcare providers, who often underestimate the impact of fatigue [3]. Additional symptoms include post-exertional malaise (PEM), dyspnea, pain and sensory hypersensitivity, vasomotor, bladder, and gastrointestinal dysfunction, cognitive and sleep problems, and muscle weakness—all of which is consistent with dysautonomia [1]. Post-COVID syndrome (PCS) refers to a cluster of symptoms that persist or emerge after the acute phase of SARS-CoV-2 infection [4]. Overlapping symptoms and shared pathophysiological mechanisms, particularly autonomic dysfunction, have become increasingly evident between ME/CFS and PCS. Several authors suggest the importance of cross-fertilization of research across these conditions, including the use of mixed-cohort trials [5,6,7]. A central aspect of ME/CFS and PCS is interoception, defined as the perception of internal bodily states. Interoceptive signals underlie autonomic reflexes, motivational drives, and conscious sensations that guide adaptative behavior [8]. Disruption of interoceptive processing may therefore play a critical role in the clinical presentation of ME/CFS and PCS [9,10].

Currently, there are no disease-specific pharmacological treatments for ME/CFS [11] or PCS [12]. Non-pharmacological approaches aim to reduce fatigue and improve functional capacity through rehabilitation, anti-inflammatory measures, and dietary interventions. Low-intensity exercise with strict pacing is recommended for individuals diagnosed with ME/CFS who are improving and wish to increase activity levels [13]. Such intervention may help relieve symptoms and prevent deconditioning in ME/CFS [11] and PCS [12]. However, PEM is common and greatly narrows the therapeutic window [14]. PEM involves a worsening of symptoms after minimal physical, cognitive, emotional, or social activity, with exacerbations typically occurring 12 to 48 h later and lasting for days or weeks. Potential adverse events (AEs) therefore include PEM episodes and symptom flares, such as increased fatigue, cognitive difficulties, pain, sleep disturbance, and orthostatic intolerance. This requires careful dose titration, planned recovery, and continuous patient feedback [13]. 

Previous exercise trials in ME/CFS have reported AEs inconsistently and have often lacked patient-centered dosing approaches, undermining confidence in exercise-based rehabilitation [15,16,17]. Current clinical guidelines advise against generic graded exercise prescriptions and recommend caution, especially in severe disease [13]. In PCS, structured, remotely delivered programs, alone or combined with education, have improved quality of life and related outcomes [18,19,20,21,22,23,24,25]. Yet, reporting of AEs remains inconsistent [26]. When therapeutic programs are individualized, symptom-titrated, and closely monitored, telerehabilitation appears feasible and generally safe [26]. 

Conscious movement-based exercise, or mind–body exercise (MBE), may reduce physical activity-related AEs by fostering pacing and symptom-titrated effort. Its core feature is movement awareness and continuous appraisal of bodily sensations and context [27]. Sustained interoceptive focus may enhance interoceptive awareness in people with chronic conditions [28], enabling real-time adjustments in effort and recovery, thereby reducing the risk of PEM. Evidence suggests that MBE produces similar effects on pain and fatigue to those of low-intensity aerobic training [29], although direct head-to-head comparisons with active exercise controls remain scarce [29,30]. Meta-analyses have shown small-to-moderate reductions in fatigue with MBE in ME/CFS and PCS (SMD −0.44, 95% CI −0.63 to −0.25) [29]. Beyond physical impact, MBE incorporates benefits associated with meditation, mindfulness practices, and conscious breathing. These include analgesia through cognitive reappraisal [31], reductions in perceived stress [32], and modulation of anti-inflammatory and cytokine activity [33], as well as immune regulation and stress-buffering mechanisms [34]. Considering the well-established links between stress, sympathetic overactivation, and Hypothalamus–Pituitary–Adrenal (HPA) axis dysregulation, MBE and related practices may contribute to restoring autonomic balance [32,33]. 

Despite promising findings, key evidence gaps remain for the efficacy of telerehabilitation and MBE. Telerehabilitation is under characterized in ME/CFS, and most existing evidence derives from post-COVID cohorts. Few studies have compared MBE with active exercise interventions. Reporting of safety and AEs is inconsistent, and mechanisms such as interoceptive awareness and autonomic balance are rarely assessed. Similarly, the durability of effects beyond the treatment period is still uncertain. 

To address these gaps, this protocol proposes a three-arm, head-to-head design, with PEM-aware dosing, strict AEs monitoring, inclusion of process measures (interoceptive awareness, heart rate variability—HRV), and follow-up at 3 months. The primary aim is to determine whether an MBE telerehabilitation program reduces fatigue severity, as measured with the 14-item Chalder Fatigue Questionnaire (CFQ-14), more effectively than conventional low-intensity exercise after 12 weeks of intervention. Secondary aims are to: (i) describe safety outcomes, with a focus on AEs under a pacing and recovery strategy; (ii) assess changes in dysautonomia-related symptoms; and (iii) examine the durability of effects 3 months after intervention. We hypothesize that the MBE program will enhance autonomic balance and interoceptive awareness compared with conventional exercise, facilitating more adaptative pacing and recovery behaviors, and therefore reducing the frequency and severity of PEM. Consequently, greater improvements in CFQ-14 scores are expected in the MBE group at 12 weeks. Although low AEs rates are anticipated under careful pacing and monitoring across groups, we hypothesize that the durability of effects will depend on participants’ adherence to the program after completion of the intervention.

## 2. Materials and Methods

### 2.1. Trial Design 

A single-blind, three-arm, parallel-group, superiority randomized controlled trial will be conducted. The protocol adheres to the Standard Protocol Items Recommendations for Interventional Trials (SPIRIT) guideline [35], and incorporates the Template for Intervention Description and Replication (TIDieR) checklist [36], and the Consensus on Exercise Reporting Template (CERT) [37]. Technical patient groups from the Spanish Research Network on Post-COVID (REiCOP) contributed to protocol development, providing input on feasibility, pacing safeguards, and patient-relevant outcomes. The study protocol has been approved by the Institutional Human Research Ethics Committee (code: 2025-0180) and registered at ClinicalTrials.gov (NCT06978582). Figure 1 presents the study protocol flowchart. 

### 2.2. Study Setting

The study is decentralized and fully remote. A single coordinating center will oversee recruitment, randomization, intervention delivery, data management, and safety monitoring. No in-person visits will be required. 

The study team comprises two senior physiotherapists and certified yoga instructors with more than 10 years of experience in therapeutic yoga, one physiotherapist with over 5 years of experience in therapeutic exercise for chronic fatigue and complex pain, three researchers responsible for online assessments, and one statistician in charge of data analysis. To ensure consistency across evaluations and intervention delivery, preparatory training sessions will be conducted prior to recruitment.

### 2.3. Eligibility Criteria

Inclusion criteria are as follows: individuals aged 18–70 years who meet the Institute of Medicine (IOM) diagnostic criteria for ME/CFS [1], or have a history of confirmed COVID-19 and fulfill diagnostic criteria for PCS [4]. Participants must have access to a computer, tablet, or smartphone for videoconferencing and be able to download and use the Welltory mobile app, V. 4.37.0 (Welltory Technologies Inc., Redwood City, CA, USA) to assess HRV [38]. They should be able to maintain a seated position for at least 45 min and demonstrate fluent comprehension of Spanish. Exclusion criteria include suspected but unconfirmed comorbidities, inability to use the software required for the study (e.g., Microsoft Teams, Google Forms), and unwillingness to adopt minor daily habit adjustments.

### 2.4. Diagnosis Confirmation and Disease Duration

A prior formal ME/CFS or PCS diagnosis is not required due to very limited specialist access withing European clinical settings [39,40]. All participants must provide documentation of a prior medical evaluation reasonably excluding alternative diagnoses (e.g., post-infectious organ damage, cardiovascular or neurological disease, cancer). The research team will not perform medical diagnoses. The lead investigator will verify that participants’ medical history meets the diagnostic criteria using a structured checklist and review of available records. Disease duration will be defined as the number of months from the self-reported onset of persistent symptoms meeting diagnostic criteria to the baseline assessment. For PCS, the date of the acute SARS-CoV-2 infection will also be recorded.

### 2.5. Consent or Assent 

The lead researcher will obtain both verbal and written informed consent from all participants. They will be informed of the study aims, potential risks and benefits, and their right to withdraw at any time by notifying the research team. Each participant will be assigned with a unique identification code linked to their personal information, which will be stored securely and accessible only to one designated researcher. The consent form includes a statement specifying that collected data may be used for future research, subject to additional ethical approval. 

### 2.6. Recruitment

Recruitment will be conducted in collaboration with REiCOP and affiliated patient associations. These organizations will disseminate information about the study aims, eligibility criteria, and contact details for the research team. A call for participation will also be posted on social media. Interested individuals will contact the research team to receive an information sheet and schedule a first online meeting with the lead researcher, during which a brief structured interview will verify eligibility and provide detailed information on study procedures.

### 2.7. Sample Size

Sample size estimation considered three study groups, a one-tailed test (a larger effect size is expected in the MBE group), an α value of 0.05, a type II error (β) of 0.20 (80% power), and a precision of 6 (equivalent to a 15% change in the primary outcome, CFQ-14 total score at 12 weeks). Fatigue variance was set at 56.5 based on a previous study with a comparable population, intervention, and measurement tools [41]. Allowing for a 20% dropout rate and a design effect of 2 (due to non-probabilistic convenience sampling), a total of 147 participants (49 per group) will be required. Calculations were made using software developed by the Clinical Epidemiology and Biostatistics Unit of the Complexo Hospitalario Universitario de A Coruña, Spain [42].

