Secondary continuous outcomes (e.g., HRV, functional performance, pain, anxiety and depression, quality of life) will be analyzed using the same LMM framework. Model assumptions will be verified through residual diagnostics; if violations are detected, data transformations will be considered, or generalized LMMs with appropriate distributions (e.g., Poisson, gamma, binomial) will be applied. For categorical outcomes, between-group differences will be tested with chi-square or Fisher’s exact tests. Where adjustment for covariates is warranted (e.g., age, sex, baseline fatigue severity), logistic regression analysis will be performed, and odds ratios with their 95% CIs will be reported. No multiplicity adjustment will be applied to secondary outcomes, following common clinical trial reporting standards [56]. Pairwise post-hoc comparisons between groups and across time points will use Bonferroni correction for multiple testing. Unless otherwise specified, all tests will be two-tailed, with statistical significance set at *p* < 0.05, and results will include effect sizes and 95% CIs.

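### The trial is sized for a one-tailed, uncorrected 5% test but analysed two-tailed, so on its own sizing inputs the stated 80% power is about 70%

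*Protocol article*

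**What the plan says.** **Sizing (section 2.7).** The calculation uses "a one-tailed test (a larger effect size is expected in the MBE group), an α value of 0.05", 80% power, a difference of 6 points on the 14-item Chalder scale (CFQ-14) at 12 weeks, and a variance of 56.5. It then allows for 20% dropout and a design effect of 2, and arrives at 49 per group, 147 in total. No multiplicity allowance is mentioned.

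**Question (section 1).** The primary aim is whether MBE reduces fatigue "more effectively than conventional low-intensity exercise after 12 weeks of intervention". That is one comparison between two of the three arms, at one time point.

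**Analysis (section 2.14).** The primary outcome is analysed with a linear mixed model containing group, time and their interaction, with random intercepts. The description of that model mentions no one-tailed test. The section later states: "Unless otherwise specified, all tests will be two-tailed, with statistical significance set at" p < 0.05. It also states: "Pairwise post-hoc comparisons between groups and across time points will use Bonferroni correction for multiple testing".

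**The concern.** Sections 2.7 and 2.14 describe different tests of the same question. A one-tailed 5% test has a critical value of 1.645 and a two-tailed 5% test one of 1.960. A sample size that gives 80% power with the first gives less with the second.

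The Bonferroni sentence adds a further uncertainty. In a three-arm model, MBE versus low-intensity exercise is a pairwise group comparison, and the text does not say whether it is exempt from the correction.

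Two things are at stake. Readers will take 80% as the chance of detecting a 6-point difference with the planned test, and that figure does not apply to it. The significance threshold for the main comparison is also not pinned down: one-sided 0.05, two-sided 0.05 and two-sided 0.05/3 can each be defended from the text. That choice should be closed before outcome data are seen.

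**Working it through.** **Inputs, all from section 2.7:** variance 56.5 (SD 7.52), difference 6, one-tailed α 0.05 (z = 1.645), power 80% (z = 0.842), dropout 20%, design effect 2, 49 per arm.

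**Step 1. Reproduce the plan's figure.** For two means, n per arm = 2 × variance × (z_α + z_β)² / difference².

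- 2 × 56.5 × (1.645 + 0.842)² / 36 = 19.41
- × 2 for the design effect = 38.81
- / 0.8 for dropout = 48.5, rounded up to 49 per arm, 147 in total

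This matches exactly. (Rounding 19.41 up to 20 before inflating would give 50 per arm.) The other candidate tests do not give 147:

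- Two-sided 5%: 24.64 × 2 / 0.8 = 61.6, so 62 per arm (186).
- Two-sided 5% with Bonferroni over three pairs (z = 2.394): 32.86 × 2 / 0.8 = 82.2, so 83 per arm (249).

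**Step 2. Power of each candidate test with 49 per arm.** The effective n per arm is 49 × 0.8 / 2 = 19.6. The standardised difference is 6 / √(2 × 56.5 / 19.6) = 6 / 2.401 = 2.50. Power is Φ(2.50 − critical value).

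| Test of MBE versus low-intensity exercise | α | Power |
|---|---|---|
| One-tailed, uncorrected (section 2.7) | 0.05 | 80% |
| Two-tailed, uncorrected | 0.05 | 70% |
| Two-tailed, Bonferroni over 2 | 0.025 | 60% |
| Two-tailed, Bonferroni over 3 (the three arm pairs) | 0.0167 | 54% |
| Two-tailed, Bonferroni over 9 (three pairs × three time points) | 0.0056 | 39% |

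A noncentral t calculation gives slightly lower values: 79%, 68% and 50% for the one-tailed, two-tailed and Bonferroni-over-3 rows.

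**Step 3. Sensitivity to the design effect.** Without it, n is 39.2 per arm and the standardised difference is 6 / √(2 × 56.5 / 39.2) = 3.53. Power is 94% two-tailed and 87% two-tailed with Bonferroni over 3.

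**Step 4. Sensitivity to the model.** The figures above are for an unadjusted two-sample comparison, as in section 2.7. If the mixed model tests a difference in change from baseline, the variance becomes 2 × 56.5 × (1 − ρ), where ρ is the baseline to 12-week correlation. The article gives no ρ. Assumed values of 0.3, 0.5 and 0.7 give two-sided power of about 56%, 70% and 90% with the design effect kept at 2.

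**The case against.** **The general rule allows exceptions.** Section 2.14 says two-tailed unless otherwise specified, and section 2.7 could be read as that specification. This is weak. Section 2.7 describes only how the sample size was estimated, and the description of the primary analysis does not carry a one-tailed test over.

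**Bonferroni may not reach the primary comparison.** The correction is attached to comparisons called post hoc, in a paragraph that opens with secondary outcomes, whereas the MBE versus low-intensity comparison is prespecified. The size of the family is not defined either. This objection stands. A reader might infer that a true 6-point difference would be missed almost half the time. That needs the contrast to be inside the correction, a family of exactly three, and the design effect of 2. The text settles neither of the first two, so the 60%, 54% and 39% figures are conditional.

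**The design effect may be too cautious.** Section 2.7 justifies it by convenience sampling, which does not by itself inflate the variance of a randomised between-arm difference. Without it, power exceeds 80% even with Bonferroni over three. This also stands, as a limit on what can be concluded. Sessions in groups of up to 7–8 could cause some clustering in the active arms, but no intraclass correlation is given, so the right inflation cannot be determined. A possibly generous input does not make the stated 80% correct for a different test.

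**A smaller effect might be expected.** The 6 points are 6 / 7.52 = 0.80 SD, and section 1 says "Meta-analyses have shown small-to-moderate reductions in fatigue with MBE in ME/CFS and PCS", giving an SMD of −0.44. A reader might infer that 0.44 is the realistic target and that power is far lower. The article does not support this: it states no comparator for that estimate, so it cannot be taken as the expected difference from an active exercise arm.

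**An analysis plan may exist.** It could define the contrast in detail. It cannot follow both sections as written, because they conflict on sidedness.

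**Conclusion.** The inconsistency is real. The 147 rests on a one-tailed, uncorrected 5% test, while the analysis section sets a two-tailed default and specifies no exception for the primary test. On the plan's own inputs, and for the unadjusted two-sample comparison used in the sizing, power is about 70% instead of 80%. If Bonferroni also applies, it is about 60%, 54% or 39% for families of 2, 3 or 9.

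The conclusion is that the stated power does not belong to the planned test. It would go too far to conclude that the trial is underpowered. That depends on whether the design effect of 2 is warranted (94% two-sided without it) and on a baseline correlation that the article does not give.

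**What to change.** **Section 2.14.** Name the MBE minus low-intensity-exercise difference in CFQ-14 at 12 weeks as the single primary contrast from the mixed model, tested two-sided at 5% and outside the Bonferroni family. Keep Bonferroni for the usual-care contrasts and the other time points.

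**Section 2.7.** Keep the record of how 147 was derived, including the one-tailed basis, since that is what happened. Add the two-sided power for 147 participants: about 70% on the same inputs.

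**Cost.** The stated power becomes less favourable. The change needs wording in two sections, a registry update, and Ethics Committee approval before implementation, which section 2.15 requires for any amendment. No extra participants are needed. Section 5 reports recruitment as ongoing; the change should be made before any outcome data are analysed.

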#### 2.11.1. Primary Outcome

The primary outcome is the total score of the CFQ-14 (Spanish version) at 12 weeks (post-intervention). The CFQ-14 measures perceived physical and mental fatigue over previous weeks on a 4-point Likert scale (0 = “never”, 1 = “sometimes”, 2 = “often”, 3 = “always”), total score 0 to 42, with higher scores denoting greater fatigue. The Spanish version of the CFQ-14 has demonstrated adequate reliability and validity [45]. 

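### Section 2.7 sizes the trial for a one-tailed test, but section 2.14 tests two-tailed by default: on the plan's own inputs 147 participants give about 70% power, not 80%

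*Protocol article*

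**What the plan says.** The primary aim, at the end of the Introduction, is to compare MBE with conventional low-intensity exercise on CFQ-14 fatigue after 12 weeks.

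Section 2.7 lists the inputs to the sample size: "a one-tailed test (a larger effect size is expected in the MBE group), an α value of 0.05", 80% power, a difference of 6 CFQ-14 points (which it calls the precision), and a variance: "Fatigue variance was set at 56.5". It then inflates the result: "Allowing for a 20% dropout rate and a design effect of 2 (due to non-probabilistic convenience sampling"). The total is 147, or 49 per arm.

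Section 2.14 analyses the primary outcome with a linear mixed model containing group, time and their interaction. It does not say whether the test is one- or two-tailed, and it does not single out one between-group contrast as primary. Later in the same section come a Bonferroni correction for pairwise post-hoc comparisons between groups and across time points, and then the general rule: "Unless otherwise specified, all tests will be two-tailed", with significance at p < 0.05 and 95% confidence intervals.

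**The concern.** The two sections describe different tests of the same hypothesis. Under 2.7, the MBE versus exercise comparison spends the whole 5% error on a benefit of MBE. Under the default in 2.14, it spends 2.5% in each direction. A power figure derived for the first test does not carry over to the second.

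Two things are at stake. First, a reader of a null result would take the trial to have had 80% power for a 6-point difference, when on the plan's own inputs the two-tailed test had less. Second, the text leaves open which threshold decides the primary claim. A one-tailed p of 0.04 corresponds to a two-tailed p of 0.08, so the same data could be called positive under 2.7 and negative under 2.14. That choice should be settled before results are seen.

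**Working it through.** **Inputs (all from section 2.7).** Variance 56.5; difference 6; 80% power (z = 0.842); dropout 20%; design effect 2; 49 per arm. The critical value is 1.645 for one-tailed 0.05 and 1.960 for two-tailed 0.05.

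**Step 1: reproduce the plan's figure.** For two means, n per arm = 2 × variance × (z_alpha + z_power)² / difference².

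- One-tailed 0.05: 2 × 56.5 × (1.645 + 0.842)² / 36 = 19.41. Times the design effect of 2 gives 38.8. Divided by 0.80 gives 48.5, rounded up to **49 per arm, 147 in total**. This matches the protocol.
- Two-tailed 0.05: 2 × 56.5 × (1.960 + 0.842)² / 36 = 24.64. Times 2 gives 49.3. Divided by 0.80 gives 61.6, rounded up to 62 per arm, 186 in total (63 per arm, 189, if rounded at each step).
- Alpha divided by three gives 70 per arm one-tailed and 83 two-tailed.

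Of these, only the one-tailed test of one pairwise comparison at 0.05 gives 49.

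**Step 2: power at 49 per arm.**

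- Effective n per arm = 49 × 0.80 / 2 = 19.6.
- Standard error of the difference = √(2 × 56.5 / 19.6) = 2.40.
- Standardised difference = 6 / 2.401 = 2.499.
- Power = Φ(2.499 − critical value).

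| Test of MBE versus exercise | Critical value | Power (normal) | Power (t) |
|---|---|---|---|
| One-tailed 0.05 (section 2.7) | 1.645 | 80.3% | 79.0% |
| Two-tailed 0.05 (default in 2.14) | 1.960 | 70.5% | 68.2% |
| Two-tailed 0.05/3 (Bonferroni over three group contrasts) | 2.394 | 54.2% | 50.3% |

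The last row assumes that the Bonferroni family is the three between-group contrasts; section 2.14 does not define the family.

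**Step 3: detectable difference.** With 80% power, two-tailed 0.05 and 49 per arm: (1.960 + 0.842) × 2.401 = 6.7 points.

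**Step 4: sensitivity to the design effect.** With a design effect of 1, effective n is 49 × 0.80 = 39.2 per arm and the standard error is √(113 / 39.2) = 1.698. Two-tailed power is Φ(6 / 1.698 − 1.960) = 94.2%, or 87.3% with the three-contrast Bonferroni threshold.

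**The case against.** The strongest reply is that 2.14 allows exceptions, and that 2.7 specifies a one-tailed test tied to the primary outcome. On that reading nothing conflicts. It deserves weight, and it makes this a less direct contradiction than two flat statements would be. It does not settle the matter. Section 2.7 describes what went into the sample size estimation, whereas the paragraph that defines the primary analysis names no one-tailed test. If the exception were intended, the primary claim would be decided at 5% in favour of MBE, twice the rate in that direction under the two-tailed rule, and a significant one-tailed result could stand beside a 95% interval that includes zero. The only reason given is that a larger effect is expected with MBE. That does not make a result in the opposite direction uninteresting in a trial where post-exertional worsening is a central concern.

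A second reply is that the design effect of 2 is a margin, which the plan justifies only by convenience sampling, and that the mixed model may gain precision from the baseline measurement. Both are fair. The first moves two-tailed power to about 94%; the second cannot be quantified, because the protocol gives no correlation. A reader might infer from the 70% that the trial is underpowered, and the documents do not support that. They support a narrower statement: the plan uses the factor of 2 to reach 147, so its power statement has to use it too.

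A reader might also infer that the 15% attached to the 6 points is an error, since 6/42 = 14.3% of the scale range. Section 2.7 does not say that the scale range is the denominator, and the calculation uses 6 in any case. No correction is warranted.

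A separate analysis plan may exist. It could state the sidedness of the primary test, but it would not make the 80% in 2.7 apply to a two-tailed test.

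**Conclusion.** The point holds as an inconsistency between sections. The arithmetic behind 147 is correct for the test assumed in 2.7, but that is not the default test in 2.14. For the two-tailed test the stated power is about 10 percentage points too high: 70.5% by the normal approximation, or 68.2% by the t distribution.

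If Bonferroni over three group contrasts applies to MBE versus exercise, the figure is about 54%. As printed, nothing exempts this contrast from the correction.

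All of this is conditional on the plan's variance, difference, dropout and design effect, with no allowance for a gain from baseline. It describes the plan's own calculation, not the trial's true power.

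**What to change.** In section 2.14, name MBE versus low-intensity exercise on CFQ-14 at 12 weeks as the single primary contrast, tested two-tailed at 0.05, and state that it lies outside the Bonferroni-corrected post-hoc set.

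In section 2.7, delete the one-tailed wording. State that, under the design effect of 2, 147 participants give about 70% power for a 6-point difference or, equivalently, 80% power for about 6.7 points. If the investigators prefer to keep Bonferroni for this contrast, state about 54% instead, with the number of contrasts that the correction covers.

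Enrolment should stay at 147. The cost is a few sentences of protocol text, submitted as an amendment under section 2.15, and a less favourable stated power. By the dates in section 5, recruitment runs to the end of January 2026, and section 2.9 keeps the analyst blinded, so the change can be made before results are known.
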